### Sampling technique

Consecutive sampling. Patients who comply with the selection criteria will be invited to participate in the study as they are identified and captured by the field researcher entrusted with this task.

Sampling will be carried out by a department specialist from the Physical Medicine and Rehabilitation department.

### Blinding

Following the assignment of the interventions, these results will be hidden from the evaluator, who is a final year medical resident specializing in Physical Medicine and Rehabilitation (AJ), who will also monitor the data and data analysts (LA and J), who will not receive information on which of the treatments corresponds to the distinct data.

The party responsible for the random assignment and participant capture will inform the evaluator and the participants of the distinct dates of results assessment for each of them, and they will be reminded of the same and will have this information confirmed (or modified) via telephone on the preceding days.

Participants will attach the protocol follow-up sheet, registering any adverse effects, if occurring, as well as drop outs, losses and causes for the same.

Study revision by part of the research team is ongoing, through the use of the new technologies and a formal quarterly meeting.

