**Methods:**

Controlled, randomized clinical trial with dual stratification, two parallel arms, longitudinal and single blind. 64 women with breast cancer-related arm lymphedema will take part in the study. The experimental group intervention will be the same for stage I and II, and will consist of neuro-dynamic exercises oriented to the activity, proprioceptive neuromuscular facilitation activities and proprioceptive anti-edema bandaging. The control group intervention, depending on the stage, will consist of preventive measures, skin care and exercise-prescribed training in the lymphedema workshop as well as compression garments (Stage I) or conservative Complex Decongestive Therapy treatment (skin care, multi-layer bandaging, manual lymphatic drainage and massage therapy) (Stage II).

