**Limitations:**

The authors have proposed the assessment of the experimental treatment for stages I and II. One possible limitation is the lack of awareness of whether or not this treatment would be effective for other stages as well as the concern for proper hand cleansing during use of bandages, given the current COVID-19 pandemic situation.

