Studies have suggested the incorporation of proprioceptive neuromuscular facilitation elements (PNF) with traditional methods of manual lymphatic drainage (MLD), to facilitate the treatment process for lymphedema patients, since they induce powerful synergic effects on edema volume, range of motion (ROM) of the shoulder, pain and depression [25]. Their independent or combination use with laser treatment has also been suggested, since improvements were also found in these variables and even in the rate of blood circulation in the underarm [26]. Also, in a study in which bandaging was not used, CDT was combined with PNF and respiration, reducing the lymphedema and also improving ROM [27], which could potentially improve activity performance, participation level and thus, quality of life [14, 28].

In response to the evidence regarding the use of the Coban®3 M bandage as an early precursor to pressotherapy in the rehabilitating treatment of lymphedema to reduce prolonged edema (the causal agent of multiple complications and functional loss) [18, 29–31], we propose the possibility of testing the effectiveness of similar bandages, but ones that avoid compressive syndromes, decrease pain and edema, promote the development of ADL and improve the treatment’s cost-effectiveness [32, 33]. We suggest combining its use with the three previously mentioned techniques (healthcare education/patient training, neuro-dynamic activities geared to neuro-muscular use and proprioceptive neuro-muscular facilitation oriented towards ADL) and which, collectively, are referred to as “TAPA” (in Spanish, Activity-oriented proprioceptive antiedema therapy).

Given the consensus for conservative lymphedema treatment, such as Complex Decongestive Therapy (CDT) or Complex Physical Therapy (CPT), we believe that comparison with our TAPA treatment should be made with this type of treatment.

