### Interventions

Following capture and recruitment, participants were randomly assigned to one of the two groups.

Both groups will receive a 3-h long healthcare education workshop on lymphedema (Lymphedema workshop), led by a department specialist in the Physical Medicine and Rehabilitation Dept. of the Clinical Inter-level Rehabilitation Management Area (MV), and offering basic knowledge on the physiopathology of lymphedema, identification of symptoms, preventive skin care measures, ADL orientation, including physical activity and recommendations for neck and arm anti-edema exercises and postures to be carried out at least once daily.

The interventions used for the Experimental group will be the same for stage I and II, and will receive 10 sessions (2 per week), of 30 min each, led by an Occupational Therapist from the Córdoba and Guadalquivir health district (MN):

− 10-min neuro dynamics oriented to the activity.

− 10-min proprioceptive neuromuscular facilitation activities.

− 10-min proprioceptive anti-edema bandaging, including patient and/or caretaker instructions for placement, as well as assistance on techniques to use for performing everyday activities.

Proprioceptive anti-edema bandaging will be placed after carrying out the neuro dynamic and neuromuscular facilitation activities. Cohesive elastic bandages will be used, containing a high content of cotton and anti-slip.

The Control group intervention, depending on the stage, will be led by a physiotherapist from the Reina Sofía Hospital in Córdoba, and will consist of:

Stage I:

- Preventive measures, skin care and exercise prescribed by the rehabilitation physician and training in the lymphedema workshop.

- Compression garments.

-Duration of 5 weeks.

Stage II:

Ten sessions of 60 min of conservative treatment of Complex Decongestive Therapy (the literature does not refer to specific protocols to quantify session duration, therefore, expert opinions based on everyday practice were used as a reference):

-Skin care.

-Multi-layer bandaging.

-Manual lymphatic drainage.

-Massage therapy (22).

Participants will be notified that during the intervention and follow-up period, they may not undertake other treatment for their BCRAL and, in the case of being subject to experimental treatment and not achieving the expected edema reduction, they may complete standard treatment upon study completion.

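### The only stated route for recording adverse effects and reasons for leaving is a sheet that participants attach, which is likely to under-record both among women who stop

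*Protocol article*

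**What the plan says.** The rule on harms and losses is one sentence in the protocol article, Methods, Blinding: "Participants will attach the protocol follow-up sheet, registering any adverse effects, if occurring, as well as drop outs, losses and causes for the same". No staff member is named as asking about harms. No times for asking are given, and nothing is said about contacting a woman who stops coming.

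Other parts of the article bear on the point:

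- **Telephone contact (Blinding).** The party responsible for assignment and capture sets the assessment dates, and those concerned "will have this information confirmed (or modified) via telephone on the preceding days".
- **Blinding.** The Abstract describes the design as "Controlled, randomized clinical trial with dual stratification, two parallel arms, longitudinal and single blind". The Blinding section hides allocation from the evaluator and the data analysts, and does not say that participants or therapists are blinded.
- **Contact during treatment (Interventions).** The TAPA group, in both stages, "will receive 10 sessions (2 per week), of 30 min each". Stage II control has "Ten sessions of 60 min of conservative treatment". Stage I control has a five-week period with exercise, skin care and garments, and no number of sessions is stated.
- **Limb findings (Table 2).** Inspection and palpation with photographs cover skin lesions, nail lesions and induration. Pain, heaviness and tension are scored from 0 to 10.
- **Timing (Statistical analysis; Interventions).** Both arms are measured at baseline, at the end of treatment, and one and three months later.
- **Other forms (Information sources).** A data collection form and a procedures manual are announced.

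**The concern.** A sheet that depends on the participant works least well for the participant who has left. A woman who stops because a bandage or garment caused trouble is the one whose adverse effect and reason matter most. She is also the one least likely to hand the sheet in.

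Two things are at stake. The first is the comparison of harms between arms. The article names local risks itself: the Background wants bandages that are "ones that avoid compressive syndromes, decrease pain and edema, promote the development of ADL", and the Limitations mention "the concern for proper hand cleansing during use of bandages, given the current COVID-19 pandemic situation". The second is the reading of the efficacy result. The Statistical analysis section fills missing values with the last available observation. Without a dependable reason for leaving, nobody can judge whether a carried-forward volume belongs to a woman who left because of the treatment.

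**Working it through.** **1. The plan's own figure.** From Sample size: mean reductions of 20% and 5% (difference 15 points), SD 20%, alpha 0.05 two-sided, power 0.80.

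- Normal approximation: n = 2 × (1.960 + 0.842)² × (20/15)² = 2 × 7.85 × 1.778 = 27.9, so 28 per group. The two-sample t-test gives 28.9, so 29 per group, as stated.
- Drop-out: 29 × 1.10 = 31.9, so 32 per group and 64 in total, as stated. (Dividing by 0.90 instead gives 32.2, so 33.)

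The present point does not depend on this calculation. It is used only for the expected number of losses.

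**2. Women whose record is most exposed.** 10% of 32 = 3.2 per arm, and 10% of 64 = 6.4 in total. This counts women expected to leave. It does not count missing records, since some may report something before they go.

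**3. What the other data cover.** Table 2 set against the harms that the article itself raises:

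| Harm or event | Recorded in both arms? | Limit |
|---|---|---|
| Skin lesion, nail lesion, induration | Yes, by inspection | Attenders only, at four time points |
| Pain, heaviness, tension | Yes, 0 to 10 scales | Same |
| New limb infection | No item | Infection appears only among the complications in Table 1 |
| Compression symptoms | No item | Nerve lesion appears only in the same Table 1 row |
| Bandage or garment removed early, and why | No item | Adherence is a percentage of prescribed activities, without a reason |

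No assessment common to both arms falls between baseline and the end of treatment. A lesion that appears and heals in that interval can be missed by the inspection.

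**4. Scheduled therapist contact.**

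- TAPA, both stages: 10 × 30 min = 5 h. At two sessions a week this is 10/2 = 5 weeks.
- Control, Stage II: 10 × 60 min = 10 h.
- Control, Stage I: 5 weeks, no sessions stated.

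The cost item in Table 2 offers 5, 10 or another number of therapist hours. It does not settle what Stage I control receives.

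**5. Why no bias is quantified.** If the true harm rate is the same in both arms and the chance that a harm is recorded is c1 in one arm and c2 in the other, the ratio of recorded rates is c1/c2. The documents give neither a harm rate nor a sheet-return rate. Any figure put in for c1 and c2 would simply come back out as the answer.

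**The case against.** The strongest reply is that the sentence is loosely worded and says little about the real procedure. Read literally, a lost participant registers her own loss, which makes little sense. The sheet may well be one that staff keep for each woman. The text does not call it the sole source, the procedures manual is not shown, and a condensed article often leaves such detail to the full protocol. The sentence also says that drop-outs and their causes are registered. Skin lesions and pain are already collected in both arms by a blinded evaluator. Neither safety nor comfort is among the specific objectives or the expected results.

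Much of this stands, and it rules out three stronger readings that a reader might infer:

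- **That harms in women who leave are definitely lost.** The documents support a likely risk under the literal reading, and no more.
- **That harms are ascertained unequally between arms.** The same sheet and the same assessment times apply to both. Unequal opportunity to report in Stage I is an inference from the contact schedule.
- **That Stage I controls have no therapist contact.** The article says that a physiotherapist leads the control intervention and gives no session count for Stage I. None stated is not the same as zero.

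The reply does not remove the point. The article goes beyond leaving harms to another document: it states a route and ties it to the participant. If a staff-kept sheet was meant, the sentence still does not say who asks, when, or who finds out why a woman did not return. The Table 2 items do not reach non-attenders.

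**Conclusion.** The point holds in a limited form. The one stated route for adverse effects, losses and causes is badly fixed: as written, it is least reliable for women who stop, about 3 of 32 per arm and about 6 of 64 overall at the planned drop-out. The four-visit limb inspection and the symptom scales fill part of the gap for attenders. They do not cover new infection, compression symptoms or early removal of the bandage or garment. A difference in opportunity to report in Stage I is plausible but not shown.

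This rests on three assumptions: that the sentence means what it says, that the unseen form and manual do not already supply active questioning, and that drop-out is near 10%. The size of any under-recording or imbalance cannot be derived from the documents. The matter is worth correcting because the correction is cheap. It is not a demonstrated bias in the trial.

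**What to change.** Use the telephone contact that already precedes each assessment. There are three post-baseline assessments, so three contacts per woman.

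- The allocating party, not the blinded evaluator, reads the same short scripted list to every woman in both arms, covering the time since the last contact: skin lesion, limb infection, numbness or tingling or another compression symptom, increased pain, and bandage or garment removed early and why. The passive wording under Blinding does not expressly name the caller, so name this person.
- The same person telephones each woman who does not attend and records the reason for leaving.
- Keep the participant sheet as a supplement, and reword the sentence to say who completes it.
- Report events by arm within stage.

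The cost is about a page in the procedures manual and a few minutes on calls already planned, plus a call to each non-attender. It needs no new staff or visits. There are two downsides. Solicited questions will raise the counts in both arms. The caller knows the allocation, so the script must be fixed and read the same way to everyone. The first call also relies on recall over the treatment period, which is a further reason to keep the sheet.

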### Study variables and measurement instruments

The study variables are shown in Tables 1, 2, 3.

**Table 1 Tab1:** Independent study variables and their measurement instruments

INDEPENDENT VARIABLES (Sociodemographic and clinical variables)	MEASUREMENT INSTRUMENTS (to be filled in with information from interviews and clinical records)
- ID: Identification number for the study (1, 2, 3...)	ID:
- Age.	Date of bird _/_/_ _ years old
- Group (Treatment carried out):	TAPA / standard.
- Work activity:	Working (Which?) /Retired/Unemployed/Others (Which?)
- Menstrual situation:	Pre-menopausal/Post-menopausal
- Laterality:	Right/ left/Both
- Body mass index (BMI): - Obesity:	BMI: height/weight^2^ yes (BMI > =30)/ no (BMI < 30)
- AHT (Arterial hypertension):	Yes (> = 120/80 mmHg/take medication) / no (< 120/80 mmHg)
- DLP (Dyslipidemia):	Yes (> = 200 mg dl/take medication) / no (< 200 mg/dl)
- DM (Diabetes):	Yes (> = 126 mg dl/take medication) / no (< 126 mg/dl)
- Heart disease:	Yes / no
- Kidney failure: Yes / no	Yes / no
- Vascular disease: Yes /no	Yes / no
- Thyroid disease: Yes / no	Yes / no
- Pacemaker: Yes / no	Yes / no
- Electro-stimulator: Yes /no	Yes / no
- Date of BC diagnosis	_/_/_
- Date of lymphedema diagnosis	_/_/_
- Stage:	I, II
- Edema location:	Hand(H)/Forearm (F)/Arm (A)/ Breast H + F/ H + F + A/ F + A/ Complete/ Others (this category should be thoroughly considered)
- Breast:	Right/ left
- Date of surgical intervention:	_/_/_
- Type of tumor: - Intervention type: Conservative/mastectomy	ductal infiltrating/in situ/ lobular/ inflammatory/tubular/other (which?): Conservative/mastectomy
- Axillary surgery:	sentinel ganglion biopsy (SGB)/ lymphadenectomy /Both/none
- No. of excised ganglia:	N°
- No. positive ganglia:	N°
- Complications:	Infection/ hematoma/ seroma/nerve lesion/Axillary web syndrome
- Chemotherapy:	Yes / no
- Radiotherapy:	Yes / no
- Hormone therapy:	Yes / no
- Immunotherapy:	Yes / no
- Breast reconstruction:	Yes / no Yes: - Type of reconstruction: Prosthesis/back/ abdomen - Reconstruction time: Immediate/ deferred
- Date of symptom onset:	_/_/_
- Lymphedema:	Right/ left

**Table 2 Tab2:** Primary dependent study variables and their measurement instruments

PRIMARY DEPENDENT VARIABLES	MEASUREMENT INSTRUMENTS/INTERPRETATION OF RESULTS
- Treatment adherence:	- yes/no Calculation of the percentage of treatment compliance for therapeutic adherence. PC = number of activities performed by patient/number of activities prescribed by the therapist *100. If PC is equal to or over 80%, it is considered that there was good treatment adherence. If less, no.
	-Physical state of the limb (inspection and palpation of the affected area). Photographs will be taken of the limb [42].
- Skin hydration: - Skin lesions: - Nail lesions: Yes / no - Induration / Fibrosis: Yes / no - Pitting edema: Yes / no - Stemmer: Yes / no	Normal/ dry/sweating Yes / no Yes / no Yes / no Yes / no Yes / no
	-Visual analogue scale (VAS), where 0 is no pain, heaviness or tension and 10 is maximum pain, heaviness or tension.
- Pain: - Heaviness: - Tension:	VAS 0–10 VAS 0–10 VAS 0–10
- Shoulder joint rotation:	Degrees with goniometer: Flexion___/Abduction___/External rotation___
	-Volume, through circometry (manual measurement of perimeters of the limbs with a tape measure, the value of the volume is approximate and volume is calculated using the Kuhnke formula Vol = (C1 2 + C2 2 + … Cn 2)/ π)) [43–45].
- Degree of lymphedema (according to % of volumetric):	_Grade 1 or mild: difference in circometry less than 4 cm (in volume 10–25%) with respect to the healthy arm. _Grade 2 or moderate: difference in circometry between 4 and 6 cm (in volume 25–50%) with respect to the healthy arm.
- Volumetric %: - Difference in volume in % between both extremities: - Volumetric in ml:	Vol = __% D = __% Vol = __ml *an edema reduction of 150 ml over the basal value is required in order to be considered clinically relevant
- Function of the upper limb/activity performance.	- Value of Quick Disabilities of the Arm, Shoulder and Hand (Quick DASH) [21], with transcultural, reliability, validity and sensitivity adaptation to changes of its extended version in 2006 [46, 47]. - Quick DASH value = __% (the result is calculated as a percentage, the higher the obtained result, the greater the disability or symptom)
- Treatment costs	Sum of expenses: -Prescription of compression garment: Yes (specify type and cost ______________) / NO - Type of bandaging used: proprioceptive / multi-layer (number of rolls used per price of each of the same) - Total number of treatment hours with therapist: 5/10/other (which:___) (number of hours used per professional hour price)

**Table 3 Tab3:** Study secondary dependent variable and its measurement instruments

SECONDARY DEPENDENT VARIABLE	MEASUREMENT INSTRUMENTS/INTERPRETATION OF RESULTS
-Health related quality of life (HRQOL).	- Value of Upper Limb Lymphedema 27 (ULL-27), specific instrument for patients with Breast Cancer-Related Arm Lymphedema, transculturally adapted and validated in its Spanish version in 2016 [48]. (The result is calculated as a percentage of social, physical and psychological dimensions in which the higher the result obtained, the greater the disability or symptom/poorer the HRQOL). - Health Questionnaire EQ-5D-5L by EuroQol Group, generic and standardized instrument used to describe and value the HRQOL of a group or population and validated in Spain by Badia X. et al. in 1999 [49]. Numeric value between 3 and 45, in which the higher the score, the poorer the HRQOL.

### Information sources

A data collection notebook/form will be created, which will be accompanied by a procedures manual.

The following instruments will be used for the measurement (Table 2), comparison and treatment of dependent variables:

### Statistical analysis

Analysis is performed for intent to treat. Data lacking after the basal measurements are replaced using the last available observation. Quantitative and qualitative variables will be described as usual (mean, standard deviation; proportions). An analysis of basal comparability of the sociodemographic and clinical variables **(**Table 1**)** will be carried out between both treatment groups. Then, a bivariate analysis will be conducted, previously verifying that the quantitative variables follow a normal distribution, using the Kolmogorov-Smirnov or Shapiro-Wilk tests, in which case, a repeated measures ANOVA is carried out (Mixed Models), to analyze the profile of patients from the basal measurement (24–72 h before treatment onset), after completing 10 sessions and one and 3 months later. If the variables do not follow a normal distribution, non-parametric tests will be used (Friedman’s test). In addition, a multivariate analysis will be performed, as well as a survival analysis, Cox regression or multiple linear regression, taking into account the examined sociodemographic and clinical covariables resulting statistically significant following the bivariate analysis, for their inclusion in the model or to be controlled for, given their potential confounding effect. The main dependent variable will be the reduction of volume of the affected extremity. Statistical analysis will be performed using the Statistical Package for the Social Sciences (SPSS v.17). Statistical significance values will be those normally used (*p* < 0.05) and bilateral contrasts will be carried out. To evaluate effectiveness, a comparative analysis of economic costs of both treatments will be performed.

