## Background

Breast cancer (BC) is a major public health issue, being the most common global cause of cancer-related deaths in females and the second most common form of cancer, with over 2 million new cases occurring in 2018 [1]. BC survival rates have improved notably over the past 20 years (survival from this type of tumor increases by 1.4% annually) [2]. BC survivors face challenges in their activities of daily living (ADL), as a result of both the illness and the subsequent treatments undertaken. These challenges include altered sensory and pain functions and neuromusculoskeletal and movement-related alterations, as well as alterations of the skin and related structures. These symptoms tend to continue for extended periods of time and therefore, BC survival has been categorized as a chronic illness with new challenges arising for rehabilitation services [3, 4].

It is estimated that more than one out of every five women treated for BC will develop lymphedema in an upper extremity (20% in 6 months, 36% in 1 year and 54% within 36 months). The most relevant risk factors are the number of lymph nodes excised in surgery, radiation therapy and obesity. This is a chronic and progressive disorder that causes edema, skin changes (which may cause fibrosis and deformity), pain, sensitivity alterations, fatigue, limitations in joint rotation, recurrent infections, an inability to independently carry out ADL, low self-esteem, etc. Although it has been recognized for years now, consensual treatment dose programs have yet to be established [5].

Tertiary prevention in BC attempts to combat the consequences of this illness. It includes aspects such as rehabilitation, relapse prevention, early diagnosis of second malignancies, management of late complications through treatments and emotional support. This type of assistance has been traditionally presented for some time now in specialized health care, but it is currently becoming an increasing primary care responsibility [6, 7].

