### Specific objectives

To measure the decrease in volume of the affected limb treated with TAPA and the maintenance of the effect over time (1 month and 3 months).To evaluate its effect on the performance of activities of daily living (ADL).To evaluate its effect on health-related quality of life (HRQOL).To determine efficiency in terms of simplicity of handling and economy of the anti-edema bandage technique used in the TAPA group.

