### Sample size

It is agreed that a decrease in the volume of the clinically relevant lymphedema may be established at 150 ml. (minimal detectable value) [39], 20% with respect to the baseline. Based on data from the literature on means and standard deviations [25, 40], for an alpha error of 0.05 and a statistical power of 0.80, the necessary sample size would be 29 subjects per group (calculation performed with EPIDAT 4.2). It is assumed that the standard treatment effect in the control group will lead to a reduction in arm volume by an average of 5%, the treatment effect in the experimental group will cause an average reduction in arm volume of 20%, and the standard deviation will be similar in both groups, approaching 20% [41]. Taking into account the dropout rate of 10% in each group, the corrected sample size is 64 patients, randomly assigned to two groups with 32 patients each.

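### Carrying the last observation forward builds in the 1- and 3-month maintenance that the trial sets out to measure; the bias is modest at the planned dropout, has no fixed direction, and is cheap to remove

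*Protocol article*

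**What the plan says.** All of the following is in the protocol article.

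- **Missing data** (Statistical analysis): "Data lacking after the basal measurements are replaced using the last available observation". The rule covers every outcome, not only volume. No justification, alternative or sensitivity analysis accompanies it.
- **Population** (Statistical analysis): "Analysis is performed for intent to treat".
- **Outcome and visits** (Statistical analysis): "The main dependent variable will be the reduction of volume of the affected extremity". It is measured at baseline and then "after completing 10 sessions and one and 3 months later". The section does not say which visit is primary.
- **Model** (Statistical analysis): if normality holds, "a repeated measures ANOVA is carried out (Mixed Models), to analyze the profile of patients from the basal measurement"; if it does not, Friedman's test.
- **Objective** (Specific objectives): the first objective covers the volume decrease and "the maintenance of the effect over time (1 month and 3 months".
- **Disease course** (Background): "This is a chronic and progressive disorder that causes edema".
- **Planning values** (Sample size): mean reductions of 20% (experimental) and 5% (control), SD about 20%, 10% dropout per group, 64 patients.

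**The concern.** A patient seen at the end of the 10 sessions and then lost has that volume copied to months 1 and 3. Change after treatment is then zero by construction, which is perfect maintenance, the very quantity the follow-up visits exist to estimate. The article itself calls the condition chronic and progressive, so no change after treatment stops is not a neutral assumption.

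A patient lost before the end-of-treatment visit has only a baseline value to carry, and is recorded as having had no reduction at any visit.

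In both cases the filled-in values enter the analysis as though they had been measured. At stake are the size of the 3-month difference and its stated precision.

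**Working it through.** **1. The plan's own sample size.** With a difference of 20 − 5 = 15 points, SD 20, two-sided alpha 0.05 and power 0.80, the normal approximation gives 2 × [20 × (1.960 + 0.842) / 15]² = 27.9, so 28 per arm. The two-sample t-test gives 28.9, so 29, which matches "for an alpha error of 0.05 and a statistical power of 0.80, the necessary sample size would be 29 subjects per group". The total of 64 follows from 29 × 1.10 = 31.9, so 32 per arm. (29 / 0.90 would give 33 per arm; nothing below turns on this.)

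**2. Loss after the end-of-treatment visit.** Let m be the end-of-treatment mean reduction (20 or 5), f the share of it lost by month 3, and q the dropout share. *Assumptions:* f is the same in both arms, and leavers resemble stayers on average.

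- True month-3 arm mean: (1 − f)m
- Carried-forward arm mean: (1 − q)(1 − f)m + qm
- Bias in the difference: f × (20 × qE − 5 × qC), where E is experimental and C is control

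The article gives no value for f, so a range is shown. The 10%/10% column uses the plan's dropout; the other two columns are hypothetical.

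| f (assumed) | True difference | 10% / 10% | 20% / 10% | 20% / 5% |
|---|---|---|---|---|
| 0 | 15.0 | 15.0 | 15.0 | 15.0 |
| 0.25 | 11.25 | 11.6 | 12.1 | 12.2 |
| 0.50 | 7.5 | 8.25 | 9.25 | 9.375 |
| 1.00 | 0 | 1.5 | 3.5 | 3.75 |

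At the planned dropout the bias is 1.5 × f, so 0 to 1.5 points. Put another way, a true 50% loss of effect appears as 45%, and a true 100% loss as 90%.

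**3. Loss before any follow-up.** Baseline is carried, so each arm mean is multiplied by (1 − q). With 10% per arm and the effect fully kept, 15 becomes 0.9 × 15 = 13.5. With half the effect lost, 7.5 becomes 6.75. The bias now runs against the experimental arm. At f = 0.5, with the 10% split evenly between early and late leavers, the two biases cancel: +0.375 and −0.375.

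**4. Power in the early-loss case.** The 10% of zeros change the variance to 0.9 × 400 + 0.09 × 20² = 396 (experimental) and 0.9 × 400 + 0.09 × 5² = 362.25 (control), a pooled SD of 19.5. A t-test with 32 per arm and a difference of 13.5 has power 0.78. The right comparator is not 32 complete patients, because lost patients cost power under any method. It is about 29 observed per arm with the full 15 points: 0.80. At an assumed 20% loss the figures are 12 points, SD 18.8 and power 0.71, against 0.74 to 0.76 with 25 to 26 observed per arm.

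**5. Precision.** Counting 32 per arm gives a standard error of 20 × √(2/32) = 5.00; 29 observed gives 20 × √(2/29) = 5.25. The ratio is 0.95, so the understatement is at most about 5% on these inputs, and less if earlier visits predict month 3 well.

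**6. False-positive rate.** In a simulation, the experimental mean fell from 20 to 5 by month 3 while control stayed at 5, so the true difference was zero. All loss was after end of treatment, and the within-patient correlation was assumed to be 0.7. The nominal 5% test rejected in about 5.8% of trials at 10% dropout per arm, and 8.3% at an assumed 20%.

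**The case against.** **The effect is small at the planned dropout.** This stands. With 10% per arm and half the effect lost, the error is 0.75 points; with nothing lost it is nil. Calling the disorder chronic and progressive describes its natural course, not rebound after treatment. Both arms are also advised to exercise daily, so partial maintenance is plausible. Errors of 3.5 to 3.75 points, or +23 to 25% at half loss, need dropout of 20% against 5 to 10%, which the article does not anticipate.

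**A reader might infer that the rule favours the experimental therapy.** The documents do not support that. Early loss works the other way, and the article does not say when patients are expected to leave. The Interventions section bars other lymphedema treatment during follow-up and offers standard treatment at study completion to experimental patients without the expected reduction. That could prompt some to leave early, but this is conjecture.

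**A reader might take 0.78 and 0.71 as power lost to the rule.** Most of that loss comes from patients being absent. The part due to the rule is about 0.02 at 10% loss and 0.03 to 0.05 at 20%.

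**A reader might think striking the sentence is enough, since mixed models are already named.** It is not. The model is conditional on a normality test, and the other branch, Friedman's test, would drop every incomplete patient and undercut the intention-to-treat aim. The wording could also mean a classical repeated-measures ANOVA, which drops incomplete cases too.

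**If the end of the 10 sessions is the primary visit,** only baseline can be carried to it, and the maintenance argument applies only to the later visits. This is fair, but those visits remain part of the first specific objective.

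**Conclusion.** The point holds and should be corrected, though it does not by itself undermine the trial. The article fixes a rule that, for late leavers, imputes the answer to one of its own objectives, and nothing elsewhere in the article softens it. This is a stated choice, not a detail left to an unseen analysis plan.

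At the plan's 10% dropout per arm, the 3-month difference can be off by up to 1.5 points in either direction, against a planned 15: upwards if all leavers are late and the effect is fully lost, downwards if all leave early and the effect is fully kept. These figures rest on the plan's 20% and 5% reductions, an assumed common share of effect lost, and leavers who resemble stayers. Larger errors require higher or unequal dropout, which is hypothetical. The overstatement of precision is real but slight.

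**What to change.** Replace the carry-forward sentence; do not merely strike it.

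- **Main analysis of volume:** a likelihood-based linear mixed model on observed visits, fitted by REML, with group, visit and group-by-visit terms and unstructured covariance. Include baseline in the response vector so that every randomised patient contributes. State the missing-at-random assumption.
- **Non-normality:** use this model whatever the normality test shows. If residuals are a concern, transform the outcome or use robust or bootstrap standard errors in place of Friedman's test.
- **Sensitivity analysis:** add one in which patients who leave are assumed to return towards baseline. Last observation carried forward may stay, at most as a labelled sensitivity analysis.

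The cost is analysis wording only: no extra patients, visits or clinical changes. The downside is reliance on missing at random, which the return-to-baseline analysis probes.
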